#### (2) Progression-free survival (PFS)

A period of time from the registration day to either of the day when progress was determined or the day of death from all causes (whichever is earlier). The following criteria are specified for the determination of PFS.

- ① "Progression" includes both progression in the determination of the total effect {3.8 (5) Determination criteria of time point response} and progression of the original disease based on a method other than diagnostic imaging {3.8 (7) Clinical progression}.

When the progression is determined based on diagnostic imaging, the date for which progression is recorded will be the day of the examination. In the case of clinical progression, the date of clinical determination will be recorded as the date of progression.

- ② In survival cases that are not determined to have experienced progression, the most recent day on which no progression is confirmed will be the recorded date for PFS.
- ③ When the diagnosis of progression is based on diagnostic imaging, the date recorded will be the "examination day" of the diagnostic imaging that provided "certain diagnosis" but not the day of examination where the progression was suspected as "suspicious on image". When the progression is determined clinically but is not based on diagnostic imaging, the date recorded for progression will be the day when the progression was determined.
- ④ The development of secondary cancer(s), e.g. heterochronic double cancer or heterochronic multiple cancer, will not be considered an event and will not be recorded as such, but will be considered to be PFS until another event is observed.
- ⑤ When treatment is discontinued due to the characteristics of or rejection by the patient and other treatment is implemented as an after-treatment, such cases will be handled in the same manner as the above for recording events and the endpoint, and will not be recorded at the time of discontinuation of treatment or the date of the initiation of after-treatment.

#### (3) Overall survival (OS)

The period of time from the registration day to the day of death from all causes. The final confirmation day of survival in survival cases will be the recorded date.

For cases that are lost to follow-up, the last date when survival of the patient was confirmed before becoming lost to follow-up will be the recorded date.

(4) Time to treatment failure (TTF)

A period of time from the registration day to either of the day when progress was determined, the day of death from all causes, or the day of discontinuation of the protocol treatment (whichever is earlier).

- ① The day of discontinuation of the protocol treatment is the day when the discontinuation will be determined.
- ② "Progression" includes both progression in determination of the total effect {3.8 (5) Determination criteria of time point response} and progression of the original disease based on methods other than diagnostic imaging {3.8 (7) Clinical progression}.  
When the progression is determined based on diagnostic imaging, the date recorded for progression will be the day of the examination. In the case of clinical progression, the date recorded for progression will be the day of clinical determination.
- ③ When the diagnosis of progression is based on diagnostic imaging, the date recorded for the event will be the examination day when the diagnostic imaging was performed that provided certain diagnosis, but not the day of examination where progression was suspected as "suspicious on image". When the progression is determined clinically but not based on diagnostic imaging, the date recorded for progression will be the day when the progression was determined.
- ④ When the protocol treatment is continuously implemented and there is no progression, the treatment will be discontinued on the final confirmed day of survival (the final confirmed day of PFS).

(5) Time to chemotherapy (TTC)

The period of time from the registration day to the day of first administration of chemotherapeutic drug

- ① For cases where mortality occurred before the initiation of chemotherapy, the date of death will be the recorded date.
- ② For cases that are lost to follow-up and in which implementation of chemotherapy is not confirmable, the last date when survival of the patient was confirmed before becoming lost to follow-up will be the recorded date.

(6) Response rate (RR)

The response rate is the rate of patients whose best overall response {3.8(6) Best overall response} in a target population with measurable lesions is CR or PR as a proportion of all the cases that underwent treatment.

(7) Health-related quality of life (HRQoL)

See "5.5 Survey of health-related quality of life".

(8) Adverse events (toxicity)

Adverse events that are observed from registration to the discontinuation of the protocol treatment will be evaluated in all treated cases (see "19 Evaluation and reporting of adverse events").

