## 5.9 Estimated enrollment and estimated study duration

(1) Estimated enrollment

200 or more (however, registration is to be continued during the registration period even if the target number is achieved)

(2) Estimated study duration

Study duration: Four years from November 2015 to October 2019

Of this period, the registration period is a year from November 2015 to October 2016, and the observation period is November 2016 to 3 years from registration of the last case

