- PgR positive group: PgR positive (J-score classification is 1% or higher)

Analyses of secondary outcomes will also be conducted on a by-cohort basis. For RR defined by a 2-value endpoint response, an accurate 90% confidence interval based on point estimation and the binomial distribution is calculated. Furthermore, for PFS, OS, TTF, and TTC, which are time-to-event outcomes, a survival curve will be estimated using a Kaplan-Meier method, and 90% confidence intervals of the survival rate at each event will be calculated using Greenwood's formula. The interaction effect will be analyzed for effect predictors in the same manner as that used for the primary outcomes.

Analysis of adverse events will be performed in all treated cases. Incidence rate by types and grade will be calculated for reported adverse events.

③ Analysis of HRQoL

FACT-G, Breast, and ES, which are calculated as total scores, will be calculated for the aggregate score and subdomain scores in accordance with a scoring manual to calculate the fundamental statistics at the time of each survey for all subjects.

Furthermore, cases with decreases in scores exceeding the threshold values as compared with scores at the registration will be individually identified and the maintenance rate of QoL will be calculated using MIDs identified by scales as a meaningful threshold value of decrease of QoL score at each measurement point.

Information obtained from questions about changes will be used as subjective anchoring information required for the identification of MID during the endocrine therapy, and differences from the previously established MID will be examined.

Since it is considered that the evaluation and analysis of HRQoL have no influence on the clinical benefit rate, which is the primary outcome measures of this study, analysis will be implemented immediately after the data collection (after the collection of QoL questionnaires at 3 months for the last registered case). The results of the analysis will be published as conference presentations and papers.

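### TTF rule ④ assigns a discontinuation, which is a TTF event, to patients still on treatment without progression, where censoring was evidently meant

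*Protocol*

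**What the plan says.** Protocol Section 3.9 (4) measures TTF from registration to the earliest of progression, death from any cause, or "the day of discontinuation of the protocol treatment (whichever is earlier"). Rule ① dates that third event: "The day of discontinuation of the protocol treatment is the day when the discontinuation will be determined". Rule ④ covers patients who are still on protocol treatment and have not progressed: "the treatment will be discontinued on the final confirmed day of survival", with a parenthesis that gives this day as the last confirmed day of PFS.

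The matching rules for the other endpoints are worded differently. For event-free patients, the PFS rule (Section 3.9 (2), rule ②) says that "the most recent day on which no progression is confirmed will be the recorded date for PFS". The OS rule (Section 3.9 (3)) says: "The final confirmation day of survival in survival cases will be the recorded date". Each fixes a date and creates no event.

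Section 5.10 (3) states that for PFS, OS, TTF and time to chemotherapy "a survival curve will be estimated using a Kaplan-Meier method", with 90% intervals by Greenwood's formula. Section 5.9 (2) sets the follow-up: "the observation period is November 2016 to 3 years from registration of the last case". After month 6, Section 5.4 (7) asks once a year whether treatment continues, and asks for a date and reason only if it has stopped.

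**The concern.** Discontinuation is one of the three TTF events, and rule ④ assigns a discontinuation to the patients who have had none of the three. A programmer who follows the sentence would set the event indicator to 1 on the last contact date for every patient still on treatment. TTF would then have no censored observations, although the Kaplan-Meier analysis needs to know who is censored. The error runs one way, downward, and is proportionately largest where treatment lasts longest. It would carry into the by-cohort TTF estimates and the predictor analyses of Section 5.10 (3).

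The date is a second weakness. Rule ④ treats the last confirmed day of survival and the last confirmed day of PFS as the same day. A patient can be known to be alive after the last assessment of progression, so the sentence allows two dates for one patient.

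This is not a detail left to the statistical analysis plan. The protocol has an operative rule for exactly these patients, and its wording is that of an event. An analysis plan that censored them would depart from the protocol's text.

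**Working it through.** **Text.** The status of a patient on treatment, alive and without progression at last contact, under each rule:

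| Endpoint | What the rule assigns | Event created? |
|---|---|---|
| PFS, 3.9 (2) ② | last day confirmed without progression | no |
| OS, 3.9 (3) | last day confirmed alive | no |
| TTF, 3.9 (4) ④ | discontinuation on the last confirmed day | yes, by the TTF definition |

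No other sentence in Section 3.9 (4) or Section 5.10 makes these patients censored for TTF.

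**Size.** The protocol gives no TTF figure, so there is none to reproduce, and no TTF distribution or loss rate. What follows is illustration.

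- From the protocol: one year of registration and observation to 3 years after the last registration (Section 5.9), so about 36 to 48 months per patient.
- Assumed: exponential TTF with true median m of 4 to 12 months; registration uniform over the year; independent loss at a constant rate of 0%, 10% or 20% per year.

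Step 1. Let S(t) be the true TTF curve and G(t) the probability of still being under observation at t. If last contact counts as failure, the estimated curve is S*(t) = S(t) × G(t). Since G(t) ≤ 1, it can only be lower.

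Step 2. Without loss, G(t) = 1 up to 36 months. The two codings then agree over that whole range, and so do medians of 4 to 12 months. The share still on treatment at the end is the mean of 0.5^(f/m) for f from 36 to 48, which is m/(12 ln 2) × (0.5^(36/m) − 0.5^(48/m)). For m = 12 this is 1.443 × (0.125 − 0.0625) = 9.0%.

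Step 3. With a share L lost per year, G(t) = (1 − L)^(t/12) up to 36 months. The apparent median is ln 2 / [ln 2/m − ln(1 − L)/12]. For m = 6 and L = 0.10 this is 0.6931 / (0.11552 + 0.00878) = 5.58 months. The 12-month rate becomes 0.25 × 0.90 = 0.225 instead of 0.25.

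| True median (months) | Still on treatment at end, no loss | Apparent median, no loss | 10% per year | 20% per year |
|---|---|---|---|---|
| 4 | 0.1% | 4.0 | 3.81 | 3.61 |
| 6 | 0.8% | 6.0 | 5.58 | 5.17 |
| 9 | 4.1% | 9.0 | 8.08 | 7.25 |
| 12 | 9.0% | 12.0 | 10.42 | 9.08 |

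A simulation of 400,000 patients per setting, analysed by Kaplan-Meier under both codings, agrees with these apparent medians to within about 0.03 months.

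**The case against.** The case for leaving the sentence alone is that its intent is plain. Rule ④ applies only while treatment continues, and rule ① dates a discontinuation by the day it is decided; for these patients no such day exists. The parenthesis in rule ④ points to the PFS date, which is the date used for event-free patients. The protocol never uses the word censored in Section 3.9, so its absence from the TTF rule is a matter of style, and the English may be a translation. The survey forms collect a discontinuation date only when treatment has stopped, so an analyst would have to create an event that the database does not hold. A Kaplan-Meier analysis also has little purpose if every patient fails.

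All of this stands as evidence of intent, and it limits the point to a wording error. It does not repair the rule: the text still assigns the event, nothing else states censoring for TTF, and the conflict over the two dates remains.

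Three stronger readings are tempting, and the protocol does not support them.

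- **A large bias.** A TTF analysis 6 months after the last registration (follow-up of 6 to 18 months, assumed median 6 months, no loss) would have 27% still on treatment and a 12-month rate of 0.25 × 0.5 = 0.125 instead of 0.25. The arithmetic is right, but no such analysis is planned. The only analysis brought forward is that of quality of life (Section 5.10 (3)).
- **A bias by site.** The follow-up rules are the same for all sites. Nothing suggests that some follow their patients for a shorter time by design.
- **An instruction to stop treatment.** Sections 5.1 and 5.3 (1) describe treatment as regular practice chosen by staff and patients. Rule ④ sits among endpoint definitions and reads as a dating rule. Its wording should still be reconciled with those sections.

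**Conclusion.** The point holds as an error of wording in a secondary outcome. Taken literally, rule ④ turns event-free patients into failures and leaves their date open between two days. The likely intent, censoring, is not written down.

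The size is modest at the planned follow-up. With complete follow-up and true medians of 4 to 12 months, the curve is unchanged to 36 months and so is the median. The effect is then confined to the 0.1% to 9% still on treatment at the end. It reaches the median only through loss to follow-up: 6.0 to 5.6 months at 10% per year and 6.0 to 5.2 at 20%, or 12.0 to 10.4 and 9.1. These figures rest on an assumed exponential TTF and assumed independent loss. The protocol gives no loss rate, but Section 5.4 (8) does end the survey when a change of hospital prevents it from continuing, so some loss is foreseeable. CBR and the sample size in Section 7.3, which is based on CBR alone, are unaffected.

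**What to change.** Replace rule ④ of Section 3.9 (4) with: *patients continuing protocol treatment without progression or death are censored for TTF on the last day on which they were confirmed to be on treatment and progression-free.* This settles the status, leaves a single date, and removes wording that could be read as a direction about treatment.

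The cost is one sentence of protocol text. The existing surveys already ask about treatment continuation, progression and survival, so no new item is needed. Using the word censored in the PFS and OS rules as well would be an optional clarification, since their sense is already clear.

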- D) Presence or absence and reasons for implementation of concomitantly used therapies (surgical therapy for breast cancer focus, radiotherapy for breast cancer focus, molecularly-targeted drugs other than mTOR inhibitors, chemotherapy, immunotherapy, other drugs recognized to have antitumor activity against breast cancer) for the past 3 months

(7) Survey plan at 6 months or later after the initiation of protocol treatment or after discontinuation of the protocol treatment

① Timing of survey

- A) Every year from 6 months after the initiation of the protocol treatment when the protocol treatment is ongoing at the time of 6 months after the initiation of the protocol treatment
- B) Every year from the day of discontinuation of the protocol treatment when the protocol treatment is discontinued at the time of 6 months after the initiation of the protocol treatment

② Contents of survey

- A) Continuation state of protocol treatment: Presence or absence of continuation of the protocol treatment. If it is discontinued, the date and reasons for the discontinuation {only for subjects corresponding to the criteria specified in 5.4 (7) ①-A)}.
- B) Survey of progression: Presence or absence of progression defined in 3.9 (2). When progression was observed, the date when the progression occurred was determined (not required for a subject whose progression is already reported.)

- C) Survey of after-treatment: Presence or absence of implementation of chemotherapy. If chemotherapy is implemented, the date and type of chemotherapy.
- D) Survey of prognosis: The final confirmed day of survival. In case of death, the date and cause of death.

(8) Discontinuation of survey

When a case meets one of the following criteria, the survey will be discontinued.

- ① When it is determined that continuation of the rest of the survey is not possible due to changing hospital or other reasons
- ② Withdrawal of consent
- ③ Death
- ④ When it becomes clear that the eligibility criteria are not satisfied
- ⑤ Other reasons, when it is determined that continuation of the study as a subject is not possible

---

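### Time to chemotherapy: where survival is confirmed later than chemotherapy-free status, rule 3.9 (5) ② counts unconfirmed time as event-free and can only push the curve upward

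*Protocol*

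**What the plan says.** Protocol 3.9 (5) defines TTC as "The period of time from the registration day to the day of first administration of chemotherapeutic drug". Two date rules follow.

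- Rule ①: "For cases where mortality occurred before the initiation of chemotherapy, the date of death will be the recorded date".
- Rule ② covers patients who are both lost to follow-up and without confirmable chemotherapy status: for cases "lost to follow-up and in which implementation of chemotherapy is not confirmable, the last date when survival of the patient was confirmed" is taken. The clause in full is that "the last date when survival of the patient was confirmed before becoming lost to follow-up will be the recorded date". The same words set the date for patients lost to follow-up under overall survival, 3.9 (3).

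For progression-free survival, 3.9 (2) ② uses a different principle for survivors without the event: "the most recent day on which no progression is confirmed will be the recorded date for PFS".

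Section 5.10 (3) fixes the analysis: "for PFS, OS, TTF, and TTC, which are time-to-event outcomes, a survival curve will be estimated using a Kaplan-Meier method". Results are given by cohort.

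After protocol treatment the data come from a yearly survey, 5.4 (7). Item C is "Survey of after-treatment: Presence or absence of implementation of chemotherapy", with date and type if it was given. Item D is the last confirmed day of survival. Under 5.4 (8) ① the survey stops when "continuation of the rest of the survey is not possible due to changing hospital or other reasons".

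**The concern.** A censoring date for a time-to-event outcome should be the last day on which the patient was known to be free of that event. For overall survival that is the last day known alive. For TTC it is the last day known to be without chemotherapy. Rule ② uses the first date for the second outcome, and does so in exactly those patients whose chemotherapy status cannot be established.

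If the survival date is the later one, chemotherapy may have started in between without being seen. The patient still counts as at risk and event-free over that time. This lowers the estimated rate of starting chemotherapy and lengthens the reported TTC. The error has one direction, so it does not average out over patients.

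**Working it through.** **1. The date rules side by side**

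| Outcome | Event | Date for a patient without an observed event |
|---|---|---|
| OS, 3.9 (3) | death | last day known alive |
| PFS, 3.9 (2) ② | progression or death | last day confirmed without progression |
| TTC, 3.9 (5) ② | first chemotherapy dose | last day known alive before loss |

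The TTC rule follows the OS row although its event is not death. The protocol speaks of a recorded date. I read this as a censoring date, since no event has been observed.

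**2. Can the two dates differ?** Yes, but they need not. Chemotherapy and survival are separate items of the yearly survey (5.4 (7) ② C and D). They go on separate forms (5.6, Nos. 4 and 5), due by the same date. Section 5.7 (5) lists a date of last confirmed survival. Section 5.7 (4) lists only the date and type of chemotherapy, with no date for its confirmed absence.

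**3. Direction.** The Kaplan-Meier estimate is S(t) = Π(1 − d/n). Moving a censoring date later leaves every d unchanged and can only raise n, so each factor stays equal or rises. The curve under rule ② therefore never lies below the curve censored at the last confirmed chemotherapy-free date. If the loss of information is itself unrelated to chemotherapy, the latter curve is unbiased and the difference between the two is bias.

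**4. Size.** The protocol states no TTC median, no affected share and no gap, so there is no figure to reproduce. Assumptions: exponential TTC with hazard λ = ln 2 / median; a share f whose chemotherapy status is last known at a time uniform over 0–24 months; survival confirmed g months beyond that; no deaths in the calculation. At time t ≤ 24 months:

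- at risk with known status: A = S(t) · [1 − f + f(1 − t/24)]
- at risk only because of rule ②: B = (f/24) · ∫ S(u) du, from max(0, t − g) to t
- hazard that Kaplan-Meier then estimates: λ · A/(A + B)

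Example with median 12, f = 0.10, g = 12, t = 12: λ = 0.0578 and S = 0.5. A = 0.5 × 0.95 = 0.475. B = (0.10/24) × (0.5/0.0578) = 0.036. The ratio is 0.475/0.511 = 0.93, so the hazard is understated by about 7% at that point. Integrating the reduced hazard gives 0.511 against 0.500 at 12 months and 0.269 against 0.250 at 24 months, and a median of 12.4 against 12.0 months.

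Overstatement of the 24-month chemotherapy-free proportion, in percentage points:

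| Median (months) | f | g = 0 | g = 6 | g = 12 |
|---|---|---|---|---|
| 8 | 5% | 0 | 0.38 | 0.83 |
| 8 | 10% | 0 | 0.78 | 1.70 |
| 8 | 20% | 0 | 1.66 | 3.57 |
| 12 | 5% | 0 | 0.46 | 0.92 |
| 12 | 10% | 0 | 0.94 | 1.87 |
| 12 | 20% | 0 | 1.98 | 3.87 |
| 18 | 5% | 0 | 0.46 | 0.86 |
| 18 | 10% | 0 | 0.94 | 1.75 |
| 18 | 20% | 0 | 1.96 | 3.60 |

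The range is 0.4 to 3.9 points. For a median of 12 months and 10% affected, the median is overstated by 0.3 month (g = 6) to 0.4 month (g = 12). The largest shift in the median is 1.7 months (median 18, 20%, g = 12).

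A simulation of 400,000 patients per scenario, with status lost at 3–24 months, medians of 9, 12 and 18 and gaps of 3–12 months, gave 0.2 to 3.5 points. At a gap of zero the two curves were identical.

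**The case against.** The strongest objection is that the gap will often be zero. Rule ② takes the last survival confirmation before loss to follow-up, not the last day the patient was ever known to be alive. Both items sit in one yearly survey, so the last survival report will often also be the last chemotherapy report. TTF rule ④ in 3.9 (4) likewise equates the last confirmed survival day with the last confirmed PFS day. This stands, and it makes the bias conditional. It does not remove it: the rule is written for patients whose chemotherapy status could not be confirmed, and the items have separate forms that can carry different last dates.

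The size can also be challenged. The share and the gap are assumptions. The 10% dropout in 7.3 is a sample-size allowance, not a rate of unconfirmable chemotherapy status. In the 10% scenarios the shift at 24 months is about 1 to 2 points. The planned 90% interval near 25% has a half-width of about 1.645 × √(0.25 × 0.75/50) = 10 points for a cohort of 50, or 5 points for 200 patients, ignoring censoring. This also stands.

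A reader might infer that patients who change hospital are the typical case, so that cohorts with more transfers are hit hardest. The document does not support this. Under 5.4 (8) ① the whole survey stops, prognosis included, so no later survival date is scheduled. Nor does the outcome rationale in 7.1 give TTC a special role; it does not mention TTC.

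**Conclusion.** The point holds in a limited form. Rule ② fixes the wrong kind of date for TTC and departs from the principle that the protocol itself uses for PFS. No other section corrects it. Where survival was confirmed later than absence of chemotherapy, the TTC curve is pushed upward, never downward. Where the dates coincide, nothing changes.

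It would go too far to say that the rule overstates TTC in every case; the document does not show how often the dates differ. The 0.4 to 3.9 points at 24 months rest wholly on the assumed median (8–18 months), share (5–20%), gap (6–12 months), exponential form and uninformative loss. TTC is one of seven secondary outcomes; the clinical benefit rate test and the sample size are untouched. The change is still worth making, because it removes a one-directional error at very little cost.

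**What to change.** Leave rule ① (death before chemotherapy) unchanged. Replace rule ② of 3.9 (5) with:

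*For patients not known to have died or to have received chemotherapy, including those lost to follow-up, TTC is censored on the last date on which the patient was confirmed not to have received chemotherapy.*

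That date is the last survey or visit at which absence of chemotherapy was reported, 5.4 (7) ② C. The restriction to patients not known to have died matters: without it, the sentence would also reach patients who die without chemotherapy and so contradict rule ①. Keep the last day known alive as the censoring date for OS; it may also serve as a sensitivity analysis for TTC.

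Cost: one reworded rule, and the date of last confirmed absence of chemotherapy kept on the after-treatment form, since 5.7 (4) does not list it now. Reported TTC may become slightly shorter.
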